#### Analysis

We will employ exploratory factor analysis to examine the factor structure of the NRS for preschool children. This analysis will reveal the number of factors naturally present in the data, and allow us to examine whether the responses of the items are loaded consistently on the corresponding factors. The appropriateness of factor analysis will be tested and the convergent validity of the scale will be examined by Cronbach’s alpha. The criterion validity of the scale will be examined by correlating the constructs of the scale to attitude to nature, enjoyment/happiness, psychological health, and subjective well-being; that is, outcome variables theoretically positively related to Nature Relatedness [32].

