### STAGE 1. NRS for preschool children – Constructing and evaluating a new measuring instrument

#### Hypothesis

The Nature Relatedness Scale (NRS) for preschool children is a short, reliable, and valid scale for measuring the environmental behaviours of preschool children aged 2–4 years in Hong Kong.

An understanding of children’s nature relatedness becomes more critical as the casual interaction with nature in daily life becomes less obvious. As none of the existing methods for measuring children’s attitudes and behaviours towards environment and nature have been assessed in preschool children, little is known about how they perceive and interact with the natural environment. This baseline is crucial to understanding whether health-promoting interventions targeting Connectedness to nature can be effective. We modified an existing scale for older children in our recent Play & Grow pilot study [32]. Overall, the reliability and construct validity indicated very low applicability to Hong Kong pre-schoolers (Cronbach’s alpha and inter-item correlation of most dimensions, e.g. < 0.50). In the proposed study, we will therefore employ a mixed-method approach, including the above mentioned Play & Grow pilot test (*n* = 39), qualitative interviews with parents (*n* = 10), further modification of the items, and a test of the final short 20-item NRS on children of 2 to 4 years of age (*n* = 100) in 2 different socioeconomic settings in Hong Kong. The qualitative data will lead to construction of an item pool with items representing four theoretical constructs of Nature Relatedness: (1) enjoyment of nature, (2) empathy for nature, (3) sense of responsibility, and (4) awareness of nature. We will collect a sub-sample from 110 children in this age group and explore the factor structure. Participants will be recruited through the Active Health Clinic, HKU. In addition to the Nature Relatedness items, we will include attitude to nature, enjoyment/happiness, psychological health outcomes, and subjective well-being. The Pediatric Quality of Life Inventory 兒科生活品質問卷 (Varni JW, Version 4.0- translated) [33] will be used in the survey to test the criterion validity of NRS for preschool children.

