#### Participants and randomization

Two to four year old children and their English-speaking parents will be recruited through kindergarten advertisements and via the HKU website. For continuity of delivered message, both parents in two-parent families will be invited to join. According to our pilot experience, however, we expect mostly mothers and domestic helpers to attend. The fathers will be welcome as well, but the same caregiver should fill the questionnaires. We set up a requirement of 80 % participation attendance of the same caregiver. Given the Play & Grow pilot data, 100 children in each group (*p* < 0.05 and power 0.8) will be needed to detect changes between the intervention and control groups. The WLCG children will be offered the Play & Grow programme at study completion (Fig. 3).

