#### Nature relatedness

Connectedness to nature in children will be measured using a short, age-adjusted NRS scale that will be validated in Stage 1. The scale uses a number of specific questions about environmental sensitivity, distance from home to natural areas, how often and how long the family spends in nature and what nature-related activities are done, including questions on recycling, garbage sorting and saving water.

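### Stage 1 assigns convergent validity to Cronbach's alpha, which cannot show it, and the RCT section describes the NRS with items outside the four constructs Stage 1 validates

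*Protocol article*

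**What the plan says.** Under STAGE 1, Analysis, the protocol article plans three things for the new scale:

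- Factor structure: "We will employ exploratory factor analysis to examine the factor structure of the NRS for preschool children".
- Convergent validity: "the convergent validity of the scale will be examined by Cronbach’s alpha".
- Criterion validity: "The criterion validity of the scale will be examined by correlating the constructs of the scale to attitude to nature", and to measures of happiness, psychological health and well-being.

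Under STAGE 1, Hypothesis, the item pool is to represent four constructs, listed as "1) enjoyment of nature, (2) empathy for nature, (3) sense of responsibility, and (4) awareness of nature". The same section describes "a test of the final short 20-item NRS on children of 2 to 4 years of age" with n = 100, and then says "We will collect a sub-sample from 110 children in this age group and explore the factor structure".

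The RCT's Nature relatedness section, under Primary outcomes and their assessments, says the trial will use the scale validated in Stage 1. It describes that scale as using "specific questions about environmental sensitivity, distance from home to natural areas, how often and how long the family spends in nature", followed by nature activities, recycling, waste sorting and water saving. The Power and sample size section lists connectedness to nature among the primary outcome domains.

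**The concern.** There are two separate problems, and a small inconsistency.

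First, the statistic does not match the property it is meant to show. Convergent validity requires the scale to agree with another measure of the same or a closely related construct. Alpha is computed from the scale's own items and contains no information about any other measure. If the plan is followed as written, a good alpha would be reported as evidence of convergent validity. The article also promises a reliability test, yet the only reliability statistic named in this section is labelled as validity.

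Second, the two descriptions of the scale do not match. If the RCT score includes items outside the constructs examined in Stage 1, the Stage 1 evidence does not carry over to that score. An item on home distance would also add between-family variation that the programme cannot move.

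Third, two sample sizes are given for what appears to be the same validation exercise.

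At stake is the meaning of a primary-outcome scale: what a between-group difference on it represents, and what Stage 1 can be cited as having shown.

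**Working it through.** The plan states no alpha, correlation or power figure for the NRS, so there is nothing to reproduce. The checks below are illustrations and a comparison of text.

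**1. What a given alpha can and cannot tell us.** From the protocol: k = 20 items and four constructs. Assumed: five items per construct, correlation r_w between items of the same construct, and zero correlation between items of different constructs.

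- Item pairs: 20 × 19 / 2 = 190. Within-construct pairs: 4 × (5 × 4 / 2) = 40.
- Mean inter-item correlation: r̄ = 40 × r_w / 190.
- Standardised alpha: k r̄ / (1 + (k − 1) r̄).
- For r_w = 0.5: r̄ = 20 / 190 = 0.105, and alpha = 2.105 / (1 + 2.0) = 0.70.

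| r_w (assumed) | r̄ | Alpha, all 20 items | Alpha, one 5-item subscale |
|---|---|---|---|
| 0.3 | 0.063 | 0.57 | 0.68 |
| 0.4 | 0.084 | 0.65 | 0.77 |
| 0.5 | 0.105 | 0.70 | 0.83 |
| 0.6 | 0.126 | 0.74 | 0.88 |

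With a between-construct correlation of 0.1, the total alpha runs from 0.77 to 0.84 over the same range of r_w. So a respectable total alpha is possible even when the four constructs are unrelated. It does not establish a single dimension, and it says nothing about agreement with an outside measure. This is also why alpha is better reported per subscale.

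**2. Content set side by side.**

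| RCT description (Nature relatedness) | Nearest Stage 1 construct |
|---|---|
| Environmental sensitivity | Awareness, arguably empathy |
| Recycling, waste sorting, water saving | Responsibility, plausibly |
| Nature activities done | Unclear; enjoyment at a stretch |
| Frequency and duration of outings | None: this is exposure |
| Distance from home to nature | None: this is a fixed feature of the household's location |

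The last two rows are the mismatch.

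**3. The two sample sizes.** The test is given n = 100. The factor structure is to be explored in a sub-sample associated with 110 children. If 110 is the sub-sample, it exceeds the stated test sample. If 110 is the pool, the sub-sample's own size is not given. Either way the statistical effect is small: 100 / 20 = 5.0 against 110 / 20 = 5.5 children per item. For an assumed correlation of 0.3, the Fisher-z 95% interval, tanh(atanh(0.3) ± 1.96 / √(n − 3)), is 0.11 to 0.47 at n = 100 and 0.12 to 0.46 at n = 110.

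**4. Age at the last visit.** Both stages take children aged 2 to 4. The last assessment is 12 months after a 10-week programme, so a child aged 4.0 at entry is then 4.0 + 10/52.18 + 1 = 5.19 years.

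**The case against.** The strongest reply is that this is a wording slip in a condensed article. The same paragraph plans factor analysis, checks that items load on their intended factors, and correlates the scale with outside measures, including attitude to nature. The correlation needed for convergent validity is therefore already planned under another name. On content, the RCT section says it uses the Stage 1 scale, several of its topics map onto the four constructs, and it does not say that distance enters the score. Stage 1's own hypothesis also speaks of environmental behaviours, which is wider than attitudes.

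Much of this stands. It makes the repair cheap and rules out saying that Stage 1 will fail to validate the scale. It does not remove the error: the text assigns convergent validity to alpha, and it presents distance and time in nature as content of a scale whose stated constructs have no place for them.

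A reader might go further on four points. The document does not support these inferences.

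- **Different languages in the two stages.** Stage 1 names a translated quality-of-life form by its Chinese title, and for the RCT "Two to four year old children and their English-speaking parents will be recruited". The language of the NRS is not stated for either stage, and English-speaking parents may also read Chinese.
- **Different ages.** Entry ages are the same in both stages. Only later visits of older entrants pass the 2 to 4 year range.
- **The NRS stays primary whatever Stage 1 shows.** The article puts validation before the RCT and gives no rule either way. Silence in a condensed article is not a rule.
- **A calculable loss of power.** The poor pilot reliability belongs to a scale adapted from older children, which is being rebuilt for that reason, and it was reported for most dimensions rather than a total score. No NRS effect size is stated; the sample-size example is vegetable consumption.

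**Conclusion.** The point holds in this form. Cronbach's alpha is wrongly assigned to convergent validity, which is therefore untested as labelled, although other validity analyses are planned. The RCT description of the NRS includes distance to nature and time in nature, which fit none of the four Stage 1 constructs. The figures 100 and 110 are not reconciled.

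The first part rests on no assumption beyond the definition of alpha. The table of alphas is illustrative and depends on the assumed item correlations and equal subscale lengths. The second part rests on reading the RCT description as the scale's content. If distance and time are collected alongside the scale and not scored, one sentence saying so would settle it. The 100/110 discrepancy has little effect on precision and is a matter of clear reporting.

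One limit is worth noting and no more: 12-month assessments of older entrants fall outside the age range in which the scale is validated.

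**What to change.** 1. In STAGE 1, Analysis, report alpha as internal consistency, for each subscale.
2. Name the already planned correlation with the attitude-to-nature measure as the convergent-validity test. Keep the correlations with happiness, psychological health and well-being as criterion validity.
3. In the Nature relatedness section, score the RCT outcome only on items retained in Stage 1, and make the description match the four constructs.
4. Keep distance to nature out of the score and use it as a baseline covariate; the Stage 2 analysis already allows for covariates.
5. Analyse time outdoors as a separate outcome. The RCT hypotheses already name it, so nothing of interest is lost.
6. State one Stage 1 sample size, or explain how 100 and the sub-sample from 110 relate.

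No new participants or instruments are needed. The cost is a few sentences, a slightly longer analysis and a narrower NRS score.

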### STAGE 2. Play & Grow, RCT

In the RCT, the families with 2 to 4 year old children will be randomly allocated to either the intervention group (IG) or waiting-list control group (WLCG). The intervention will comply with CONSORT [34] (Fig. 3). The program is based on the recently completed Play & Grow pilot study, which utilised elements of the three successful healthy lifestyle interventions EarlySTOPP [22], INFANT study [23] and MEND [35], with the addition of the novel Connectedness to nature element.

**Fig. 3 Fig3:**
[figure not shown]
RCT, Study design

#### Hypotheses

After completing the Play & Grow program (10-week, 6 and 12 months), *children* in the IG, when compared with the WLCG, will: (1) eat healthier, have a higher responsiveness to satiety, be less fussy with food, have less food neophobia; eat more fruit, vegetables and less obesogenic foods; (2) be more active, less sedentary and (3) have a higher Connectedness to nature, reflected in increased time spent outdoors. The *parents* in the IG will: (1) know more about healthy eating, active play and Connectedness to nature; and 2) gain *general* and *specific* parenting practices, including role-modelling for healthy habits.

#### Participants and randomization

Two to four year old children and their English-speaking parents will be recruited through kindergarten advertisements and via the HKU website. For continuity of delivered message, both parents in two-parent families will be invited to join. According to our pilot experience, however, we expect mostly mothers and domestic helpers to attend. The fathers will be welcome as well, but the same caregiver should fill the questionnaires. We set up a requirement of 80 % participation attendance of the same caregiver. Given the Play & Grow pilot data, 100 children in each group (*p* < 0.05 and power 0.8) will be needed to detect changes between the intervention and control groups. The WLCG children will be offered the Play & Grow programme at study completion (Fig. 3).

#### Power and sample size

The primary outcomes for this intervention relate to eating, active play and Connectedness to nature habits. The sample size calculation is based on a similar study conducted in New Zealand, MEND 2–4, which provides relevant parameter estimates for children aged 2 to 4 years of age [35, 36]. As there have been no similar interventions in this age group in Hong Kong, we adpoted the MEND design suggestion and calculated the sample size first of all, in regards to our primary outcomes (for example, 25 % increase in vegetable consumption), hence 100 families in each group will be required for a power of 0.8, α = 0.05 [35]. Based on the pilot data, and the dropout rate of 20 %, we intend to recruit 240 families. This sample size will be sufficient to detect medium effect sizes (power of 0.8 at α = 0.05) in our the secondary outcomes [37]. To increase retention in the study, we will build connections with the participants through a blog created for the Play & Grow pilot, and send birthday cards to each child participant.

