### Objectives

The main objective was to test the hypothesis that the proposed healthy lifestyle intervention program Play & Grow, will improve stated outcomes. The effectiveness of Play & Grow intervention, will be tested by conducting a randomised controlled trial (RCT), enhanced with the novel connectedness to nature element, and evaluating immediate and long-term health effects on participating children's active play/sedentary behaviours, zBMI eating habits (Stage 2).To validate the newly created NRS on the preschool population of Hong Kong (Stage 1)To improve general parenting practices (encouragement, positive involvement, problem solving, knowledge of child nutrition and active play, age-appropriate activities and attitudes to nature); and specific parenting practices such as outdoor playtime routines, meal and snack routines, environmental practices and (Connectedness to nature) (Stage 2)To test whether Connectedness to nature encourages healthy lifestyle routines and positively influences healthy eating and active playtime in children aged 2 to 4 in Hong Kong (Stage 2).To test if the key elements of the Play & Grow programme; that is, offering anticipatory guidance [26] and emphasizing parenting skills [23], will be beneficial for the outcomes of the intervention. Further, we assume that the added novel element, Connectedness to nature, will boost the programme and have additional beneficial effects on the children's well-being as a result of increased outdoor time and participation in activities related to nature, active play and food.

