### Primary outcomes and their assessments

Measurements will be conducted prior to and after the 10-week intervention, with further follow up assessments at 6 and 12 months in order to observe both the short and long term outcomes (Table 2). Although many variables will be measured in both children and participating parents, we carefully chose a few questionnaires, which covered multiple variables.

**Table 2 Tab2:** Intervention outcome instruments

Intervention Outcomes	Source	Baseline	End-of-intervention	6-month Follow-up	12-month Follow-up
Parent					
General Parenting Practices					
Knowledge of children’s:					
Feeding	PCFQ	✕	✕		
Nutrition	NKQ	✕	✕		
Active play	Pre-PAQ	✕	✕		
Connectedness to nature	NRS (self-developed)	✕	✕		
Correct practices:					
Feeding	CFPQ	✕	✕	✕	✕
Nutrition	NKQ	✕	✕	✕	✕
Active play	Pre-PAQ				
Connectedness to nature	NRS (self-developed)	✕	✕	✕	✕
Parental self-efficacy for correct practices	INFANT scale	✕	✕	✕	✕
Parental modelling of healthy habits, diet, active play, connectedness to nature	INFANT scale	✕	✕	✕	✕
Limit setting	Self-developed scale	✕	✕	✕	✕
Specific Parenting Practices					
Diet	CEBQ	✕	✕	✕	✕
Active Play	IPAQ, Pre-PAQ	✕	✕	✕	✕
Sedentary time	Pre-PAQ	✕	✕	✕	✕
Connectedness to nature	NRS (self-developed)	✕	✕	✕	✕
Child					
Eating Habits	EPAQ	✕	✕	✕	✕
Physical Activity	Pre-PAQ	✕	✕	✕	✕
Sedentary Behaviour	Pre-PAQ	✕	✕	✕	✕
Food Neophobia	PCNS	✕	✕	✕	✕
Connectedness to nature	NRS (self-developed)	✕	✕	✕	✕

Please see detailed references in proposal’s text

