### Secondary outcomes and assessments

Many of the MENT study assessments will be used in this RCT, since they are validated for this age and outcomes [46]. These include *Parental knowledge of nutrition* (Nutrition Knowledge Questionnaire (NKQ) [47]), *Parental behaviours related to feeding, eating and physical activity* (The Preschool Child Feeding Questionnaire (PCFQ) [48] and the Child Feeding Questionnaire (CFQ) [8]); Validated Active Australia Survey [49]; Parental encouragement and parent cognitions: 5-point Likert scales, Pliner’s Child Neophobia Scale (PCNS) [50].

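### Three primary domains are named but no primary score, visit or success rule, so the stated alpha of 0.05 and power of 0.8 belong to no identifiable test

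*Protocol article*

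**What the plan says.** All references are to the protocol article.

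- **Power and sample size:** "The primary outcomes for this intervention relate to eating, active play and Connectedness to nature habits". The size is given as "hence 100 families in each group will be required for a power of 0.8, α = 0.05". The only target is "for example, 25 % increase in vegetable consumption", and the source is named: "The sample size calculation is based on a similar study conducted in New Zealand, MEND 2–4". No mean, SD or rate is given, and no target for active play or Connectedness to nature.
- **Primary outcomes and their assessments:** measurement is before and after the 10-week programme and at 6 and 12 months. The authors write that "we carefully chose a few questionnaires, which covered multiple variables". The subsections assign EPAQ and CEBQ to eating, Pre-PAQ to activity and sedentary time, and NRS to nature.
- **Hypotheses:** children are expected to do better at all three post-baseline times. Within eating alone the list includes satiety responsiveness and "be less fussy with food, have less food neophobia; eat more fruit, vegetables and less obesogenic foods".
- **Objectives:** the main objective includes "evaluating immediate and long-term health effects", which gives early and late visits equal standing.
- **Analysis (Stage 2):** MANOVA, multiple regression, linear mixed models and a 2x3 repeated-measures ANOVA are listed. None is designated as the test that decides the trial.
- **Role of CEBQ:** the Eating habits subsection makes it a measure of the child's eating style. Table 2 lists it as the source for the parent's dietary practices.

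**The concern.** An alpha and a power figure are properties of a particular test of a particular outcome at a particular time, under a stated rule for what counts as success. This article gives the two figures and a set of outcomes, but not the link between them. A reader cannot say which result would confirm the main hypothesis, or what the chance is of confirming it wrongly.

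What is at stake is the effectiveness claim. With three domains, several scores in at least one of them and three post-baseline visits, the investigators could choose after seeing the results which one to present as the primary finding. Choosing the primary outcome and the outcome behind the sample size is protocol content. The article gives both a section of their own, so this is not a detail that condensation has dropped.

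**Working it through.** **Inputs from the article:** 3 primary domains; 3 post-baseline visits; 100 per group; alpha 0.05; power 0.8.

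**Assumptions:** two-sided tests, because sidedness is not stated; correlations between tests, because none is given.

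**1. The plan's own figure.** In the normal approximation, the standardised difference detectable with 100 per group is d = (1.960 + 0.842) × √(2/100) = 2.802 × 0.1414 = 0.396. A 25 % relative rise in a mean equals this d only if SD/mean = 0.25/0.396 = 0.63. With SD/mean of 0.5, 0.8 or 1.0, the need would be 63, 161 or 252 per group. The article gives no SD, so the 100 can be neither reproduced nor refuted, and it cannot be checked at all for the other two domains.

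**2. If any one success counts, each test at 0.05.** With independent tests the risk of at least one false positive is 1 − 0.95^k. Correlated cases come from simulated normal test statistics (400,000 draws).

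| Tests | Assumed correlation | Risk |
|---|---|---|
| 3 domains, 1 visit | independent | 1 − 0.95³ = 0.143 |
| 3 domains, 1 visit | 0.3 / 0.5 / 0.8 | 0.136 / 0.126 / 0.098 |
| 3 domains × 3 visits | independent | 1 − 0.95⁹ = 0.370 |
| 3 domains × 3 visits | 0.6 within a domain, 0.3 between domains | 0.29 |
| 3 domains × 3 visits | 0.5 between domains, 0.7 between visits (product of the two across both) | 0.26 |
| 3 domains × 3 visits | 0.8 between all nine | 0.17 |

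**3. If all three domains must succeed, each test at 0.05.** The false-positive risk stays at or below 0.05. If each domain has power 0.8, joint power is 0.8³ = 0.51 when independent, and 0.57 to 0.69 at correlations of 0.3 to 0.8. If any one success suffices, it is 1 − 0.2³ = 0.99 when independent.

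**4. If the three are co-equal and alpha is split.** At 0.05/3 the critical value is 2.394. At d = 0.396, power is Φ(2.802 − 2.394) = Φ(0.408) = 0.66. The difference detectable with power 0.8 is (2.394 + 0.842) × 0.1414 = 0.458, or about 0.46 SD. Keeping power 0.8 at d = 0.396 would need 2 × (3.236/0.396)² ≈ 134 per group.

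**The case against.** The strongest reply is that the article nowhere says each score at each visit will be tested separately at 0.05. That is right. Alpha appears only in the sample-size statements. The Analysis section lists MANOVA, which can test several outcomes jointly, and repeated-measures and mixed models, which can test across visits. A multiplicity rule may stand in an analysis plan that is not shown, so its absence here is no fault. A reader might infer that the error rate is far above 5 %, but the document does not establish this. The figures in step 2 are conditional on a procedure that the plan leaves open.

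A reader might also infer that power for the primary set is below 0.8. This is not shown either. Without a success rule it is undefined: lower than 0.8 if all domains must succeed or alpha is split, higher if any one suffices. Nor does the text say that vegetable consumption alone determined the size. It is offered as an example for primary outcomes in the plural.

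It is tempting to add that food neophobia and zBMI are classified inconsistently, since neophobia is in the child hypothesis while the "Child Neophobia Scale (PCNS" entry is under secondary outcomes, and zBMI is in the main objective but measured under secondary outcomes. This is weak. The hypotheses also cover parent outcomes, Table 2 also holds secondary instruments, and an objective may be served by a secondary outcome. Only the CEBQ mismatch is a real conflict.

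What the objection does not remove is the gap itself. A later multiplicity procedure needs a defined primary family to act on, and the listed joint methods are not designated as decisive.

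**Conclusion.** The point holds in a limited form: the primary endpoint is badly fixed. Three domains are named, with no primary score, visit or success rule, and the sample size is illustrated by one example outcome. Neither the 5 % error rate nor the 0.8 power can be attached to the primary set.

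The consequence ranges with the rule that is eventually adopted. Under an any-success rule with separate tests at 0.05, false-positive risk is about 0.10 to 0.14 at one visit and about 0.26 to 0.37 over three visits; at a uniform correlation of 0.8 the three-visit figure falls to 0.17. Under an all-must-succeed rule there is no inflation, but power is about 0.5 to 0.7 if each domain has 0.8. These ranges rest on assumed correlations and two-sided tests. The effect size of 0.396 used in step 4 is back-calculated from 100 per group, not taken from the article.

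**What to change.** Before any data are compared by group, amend the protocol and the registry entry as follows.

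1. The investigators name one score for each of the three domains and one primary visit.
2. They state the success rule. Two workable choices are:
   - a fixed testing order, each step at 0.05, starting with vegetable consumption because it is the only outcome with a stated sizing target; or
   - three co-equal outcomes under Holm, with the detectable difference restated as about 0.46 SD at 100 per group. That figure uses the first and strictest Holm step, 0.05/3, so it is conservative.
3. All other scores and visits become secondary.
4. The role of CEBQ is reconciled between the Eating habits subsection and Table 2.
5. The mean and SD behind the vegetable target are given, so that the 0.8 can be checked for that outcome.

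The cost is wording; no extra families are needed. In a fixed order, later outcomes can be claimed only if the earlier ones succeed, so the novel nature outcome may be blocked if it is placed last. Under Holm the power statement is less favourable. Either way, choosing one visit lowers the standing of the others, including any long-term effects that are not chosen.

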### The pilot programme Play & Grow

Play & Grow is a 10-week family-based, multi-component healthy lifestyle programme for families with preschool children aged 2 to 4, and was developed and tested in a pilot study (*n* = 39, aged 2.15, SD = .88, retention rate of 93 %) by the PI and her team. The aim of Play & Grow is to encourage healthy eating habits and active play in children from an early age, and to bring about healthy behavioural changes in families. The programme also includes a Connectedness to nature element designed to equip parents with environmental knowledge and skills. The generated pre- and post-test comparison data indicated the effectiveness of the programme (not presented here). A detailed manual and full resource kit were created, and each session consisted of: (i) a 15-min theoretical education component (food, activity, Connectedness to nature), and (ii) a 30-min component on indoor and outdoor nature-related activities, such as playing with objects found in nature and searching for natural treasures (Table 1). Some nature activities were food-related, such as growing plants, creating miniature indoor gardens, and healthy cooking. While the intervention group received the programme as detailed in the resource kit, the control group received an information folder containing government-recommended physical activity and dietary guidelines for children [27]. To enhance participation, all the sessions were scheduled on weekends. The outcome data was collected using a number of scales and questionnaires addessing eating, active play and nature-related habits before and after the programme, and group session debriefings were held at the beginning and end of the programme. The programme proved popular amongst participants and the results demonstrated significant positive changes on a number of health-related outcomes, such as healthier food habits and an increase in caregiver physical activity levels.

**Table 1 Tab1:** Intervention content and Anticipatory guidance topics, enhanced with connectedness to nature

Session	Activities during the pilot study
1	Welcome and Intro: Setting goals, Communication in the family. Introduce basic concepts regarding parental feeding styles and how these might relate to beliefs about parenting and safety of children. *Connectedness to nature/Outdoor play: active nature games, discovering nature, practicing awareness to sounds, touch, smells, temperature, etc.*

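### The dropout allowance is added to 200 instead of divided out: 240 recruited at 20% loss leaves 96 families per group, not the required 100, a small shortfall

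*Protocol article*

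**What the plan says.** The Power and sample size section sets the requirement: "100 families in each group will be required for a power of 0.8", at α = 0.05. It then mentions pilot data and a 20% dropout rate and ends with "we intend to recruit 240 families". The abstract gives the same total of 240. The section adds that this sample is enough for medium effects in the secondary outcomes, also at power 0.8.

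The source of the 100 per group is described in two ways. Participants and randomization says "Given the Play & Grow pilot data, 100 children in each group". Power and sample size says "The sample size calculation is based on a similar study conducted in New Zealand", and explains that no similar intervention had been run in this age group in Hong Kong.

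The section on the pilot programme reports its retention ("retention rate of 93" per cent). The Analysis section of Stage 2 plans an intention-to-treat approach, with linear mixed models for several outcomes.

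**The concern.** A dropout rate is a proportion of the families who enter. To finish with 200, the required number is divided by the proportion retained. Raising 200 by 20% gives a smaller figure, because 20% is then lost from the larger number recruited. At the protocol's own dropout rate, the recruitment target therefore does not produce the group size that the same paragraph calls required.

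What is at stake is the consistency of the only sample-size justification in the article, and the accuracy of the power attached to it. Anyone who recomputes the paragraph will find that required number, dropout and target do not fit together. A fuller protocol could not reconcile them as printed.

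**Working it through.** **Inputs, all from Power and sample size:** 100 families per group (200 in total, equal groups), power 0.80, α = 0.05, dropout 20%, target 240. Sidedness is not stated, so two-sided is assumed and one-sided is checked as well.

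**Reproducing the stated target**
- By multiplication: 200 × (1 + 0.20) = 240, which matches exactly.
- By division: 200 / (1 − 0.20) = 250, which does not match. The difference is 10 families.

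**What 240 leaves**
- At 20% dropout: 240 × 0.80 = 192, or 96 per group, 4 per group short.
- Dropout at which 240 still leaves 200: 1 − 200/240 = 16.7%.

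**Power at 96 per group**

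The article gives no standard deviation or baseline rate for its example target (a 25% rise in vegetable intake), so the 100 per group cannot be reproduced. I take it as correct and solve for the standardised difference that it implies:

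- d = (1.960 + 0.842) × √(2/100) = 0.396 (normal approximation; 0.398 with the t-test).
- Power at 96 = Φ(0.396 × √(96/2) − 1.960) = Φ(2.745 − 1.960) = Φ(0.785) = 0.784.

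The loss is 0.800 − 0.784, about 1.6 percentage points. In this formula the effect size cancels: power at 96 is Φ((1.960 + 0.842) × √(96/100) − 1.960), whatever the scale of the outcome. The loss is nearly the same under other assumptions:

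| Comparison | Power at 96 per group |
|---|---|
| Two means, normal, two-sided | 0.784 |
| Two means, t-test, two-sided | 0.784 |
| Two means, normal, one-sided | 0.786 |
| Two proportions, control rates 0.1 to 0.7 | 0.784 |

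**Secondary outcomes**

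Reading medium as d = 0.5 (an assumption): power at 96 = Φ(0.5 × √48 − 1.960) = Φ(1.504) = 0.93, well above the stated 0.8.

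**If loss were as low as in the pilot**

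At 7% loss, 240 × 0.93 / 2 = 111.6 per group, with power of about 0.84 for the same effect.

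**The case against.** The strongest reply is that nothing of substance changes. The article states power to one decimal place, and 0.784 rounds to 0.8. The calculation above discards every family that drops out and compares two groups at one time point, whereas the Analysis section plans intention to treat, baseline adjustment and mixed models. Mixed models can use data from families who leave after a post-baseline visit.

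This stands as an argument about size. It does not rescue the arithmetic. The section makes an explicit allowance for dropout, so it treats those families as lost, and on that basis the allowance is 10 families too small.

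Three stronger inferences are tempting, and the documents do not support them.

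- *That the trial fails to deliver its power.* The shortfall is about 1.6 points under a simple comparison.
- *That the other power statement in the paragraph falls as well.* At d = 0.5 it holds with a wide margin.
- *That 20% contradicts the pilot's 93% retention.* The sentence can be read as listing pilot data and 20% dropout as two separate inputs. The pilot compared measurements before and after a 10-week programme, while the trial follows families to 12 months. Allowing for more loss than the pilot saw is cautious, and at the pilot's rate 240 would be more than enough.

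**Conclusion.** The recruitment figure is wrong as derived. At 20% dropout, 240 families leave 96 per group, and 250 would be needed to leave 100. The cost is a fall in power from 0.80 to about 0.78. That figure assumes that 100 per group is correct for power 0.80, that families are independent, that the test is a two-sided two-group comparison at α = 0.05, and that dropouts contribute nothing. The standardised difference of about 0.40 is back-solved here and is not a design figure of the protocol. The claim about medium effects is untouched. The two attributions of the 100 per group are a real but secondary inconsistency of wording, with no bearing on the arithmetic. Overall this is a minor correction.

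**What to change.** Keep 240 and replace the sentence on recruitment with one of these:

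- 240 families preserve 100 per group for dropout up to 16.7%; or
- with 20% dropout, 96 families per group remain, giving power of about 0.78 for the effect that 100 per group detects with power 0.80.

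The first needs no further assumption. The second should be worded relative to the 100-per-group effect, as here, so that a back-solved standardised difference does not enter the protocol as if it had been its design basis. Recruiting 250 would also reconcile the figures, but the size of the shortfall does not call for it.

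In addition, name the same source for the 100 per group, pilot or New Zealand study, in both Participants and randomization and Power and sample size.

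The cost is one reworded sentence and one aligned attribution. Design, recruitment and analysis do not change. With the second wording, the stated power becomes slightly less favourable.
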